# II. Introduction and problem statement

Dengue is a viral vector-borne disease, predominantly affecting the urban areas but extending into more populated rural areas. The main insect vector is the highly synanthropic *Aedes aegypti* mosquito. The vector breeds in water storage containers and other deposits containing relative clean water, and bites and rests in and around human dwellings. Attempts at eradication failed during the 1960s in Latin America so today more than 50% of houses are infested with *Aedes* larvae in many endemic areas (1;2).

Dengue prevention has long depended on control of immature vector populations either by insecticidal treatment (larviciding) or removal of breeding sites and occasionally, biological control. These interventions showed a variable success and are in most of the countries difficult to sustain. Control of immature stages impacts only on vector densities and not on mosquito longevity or other key parameters affecting dengue transmission: targeting adult vectors is more likely to reduce both transmission and mosquito density. Insecticide-treated materials (ITM), highly effective in preventing malaria and other nocturnally transmitted vector-borne diseases, have shown a first proof of efficacy on dengue vector densities and potentially on dengue transmission in Venezuela and Mexico (3). These ITM are generally well accepted by communities and additionally: a) insecticide-treated curtains (ITCs) might be hung inside houses (in doorways or as screens) avoiding harmful UV light; b) other insecticides and novel biological insecticides may be safely applied to netting, thus providing a means of managing pyrethroid resistance; c) interest from new and existing industry partners will result in new products to meet future control needs. The WHO Dengue Scientific Working Group of 2006 identified the development and evaluation of ITM as a primary global research stream.

New vector control tools should be user-friendly and not require much additional work from householders; they should be affordable, safe and effective in reducing vector densities below threshold levels estimated by the "pupae per person index"(4;5). There are many examples of potentially effective disease control products that have had only limited impact on the burden of disease because of inadequate implementation resulting in poor access. Implementation research has to help ensure that proven control products have the intended health impact. Implementation or distribution of tools of public health interventions consists of different components: geographical availability of product, economical affordability, acceptability of intervention and tool, demand for intervention, distribution strategies, …

Many diurnal human activities take place outside the house (schools, factories, …) and many individuals are potentially exposed to dengue transmission away from the household, therefore these places will be included in the intervention where possible. The difficulties and opportunities of inclusion of these sites in the tested strategies will be evaluated.

***Directly addressing these aspects, we will undertake a study, investigating the interaction between an ITM distribution (adult targeting) and community-based environmental management strategy (immature stages targeting) in a municipality of Cuba, where the baseline infestation already reached low levels, but where transmission still occurs. In this project, the tools will be delivered for free, so we will focus our research on the uptake, acceptability, effectiveness and cost-effectiveness of tools with or without a combined community-based environmental strategy.***

# III. Research objectives and hypothesis

## III.A. General Objective

Evaluate the acceptance, effectiveness and cost-effectiveness of Insecticide treated curtains (ITC), as a single *Aedes* control strategy or as a combined strategy together with community-based environmental management.

## III.B. Specific objectives

1. Evaluate the acceptability and uptake of tools in the combined (ITC and community-based environmental management) and single strategies
2. Evaluate the effectiveness of ITC in the control of *Aedes aegypti* and its added effect when applied in combination with other strategies
3. Evaluate the cost-effectiveness of an ITC intervention as a single and combined strategy

# IV. Methodology

## IV.A. Description of study and Research design

A. Description of study and study areas
Area Sur and Centro of Guantanamo were identified as the areas where the study sites will be selected from. Both areas have high infestation-levels in comparison to other areas of Guantanamo municipality.

The circumscriptions (lowest geopolitical unit, containing approx. 500 houses) were identified as unit of intervention and of analysis of effectiveness.

Circumscriptions with the highest infestation –levels will be selected and afterwards the allocation to control or intervention group will be on a random basis. The circumscriptions with a common boundary will be eliminated from the study, as a certain spill-over effect is expected (3).

Design:

Cluster-randomized controlled trial, Latin square design

|  | ITC Distribution | No ITC distribution |
| --- | --- | --- |
| Assisted CB environmental management | Group Intervention 2 | Group Control 2 |
| No assisted CB environmental management | Group Intervention 1 | Group Control 1 |

*Group Intervention 1*: Distribution of Curtains, no assisted community-based (CB) environmental management

*Group Intervention 2*: Distribution of Curtains + assisted CB environmental management

*Group Control 1*: No curtains, no assisted CB environmental management

*Group Control 2*: No curtains, assisted CB environmental management

Sample size estimation (based on the effectiveness of curtains measured through entomological indices):

The cumulative house index over 1 year is estimated at 2%.

We estimate that we can decrease the infestation-levels with 75% in the ITC intervention strategy in comparison with no intervention. Based on the Hayes and Bennett sample size estimation (6), we need 6 clusters of 500 houses in each arm (‘ITC distribution’ and ‘no ITC distribution’) to demonstrate the effect of the curtain-intervention (power of 80%). The subdivision of each arm in 2 groups makes it possible to 1) measure the influence of adding an ITC strategy on top of the community involvement process and 2) the influence of community involvement on the ITC uptake.

(Annex 1)

Duration of study: Primary and secondary outcomes will be evaluated over a period of 2 years.

Outcomes:

*Primary outcome:*

Effectiveness: cumulative house index (on year basis) and other *Aedes* infestation indices

*Secondary outcomes:*

- Uptake and use of IT curtains

- Satisfaction with IT curtains

- Level of community involvement reached

- Change in intra- and extra domiciliary risk for *Aedes* infestation

- Cost-effectiveness of IT curtains

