     1. Through Focus group Discussions with community networks and inhabitants, and through in depth interviews with inhabitants purposively sampled, data will be collected using the Rifkin-tool (already adapted to local context by Dr. [name], see annex 6 & 7) (intervention and control groups).
     2. Revision of documents:
        - Coverage of community workers
        - Existence of Community network
        - Revision of needs identification and plan of action (for environmental management activities) done by Community network
        - Revision of report of activities and risk monitoring form of Community network

1. Monitoring:
   1. Entomology:
      1. The same measurements as in the baseline entomological study will be done once intervention started (House Index (HI), Breteau index (BI), Pupal Index per inhabitant (PPI)). The frequency of the surveys will be according the cycles taking place by the routine control programme, with at least one survey per month.
      2. Repeated blocks
      3. GPS geo-referenced positioning system for follow-up of foci
   2. Epidemiology of clinical Dengue cases if an epidemic presents itself in the period of study
   3. Observation of main intra and extra domiciliary risks at household level (data collection through an existing monitoring system)
   4. Uptake and use of curtain

Uptake and its seasonal variances will be evaluated every 4 months (3 X/year) over a period of 2 years. During observation-visits in all houses, these aspects will be evaluated (Observation guide: annex 8).

- 1. Registration of executed vector control activities: information obtained from community perspective (Questionnaire: annex 9)

Every 4 months, one in 30 households will be questioned concerning the vector control activities that were realized in the previous period.

.

1. Mid-term assessments
   1. Evaluation of acceptance, use and satisfaction (curtains and implementing strategy) through household surveys, 3 and 18 months after distribution (in a sample of 330 houses/intervention arm (110 houses/circumscription, systematic random sampling)) (data collection form: annex 10)
   2. Evaluation of the adoption of the model of implementation/communication: (process evaluation) through key informant interviews (18 months after distribution)
   3. Evaluation of level of involvement of community in control actions (18 months after distribution)

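### The primary outcome does not fix one index and one time window, although the sample size rests only on the 1-year cumulative house index

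*Protocol*

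**What the plan says.** All but the last of these statements stand in section IV.A of the protocol.

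- **Primary outcome:** "Effectiveness: cumulative house index (on year basis) and other *Aedes* infestation indices". The further indices are not listed, ranked or tied to a decision rule.
- **Duration:** "Primary and secondary outcomes will be evaluated over a period of 2 years".
- **Sample size:** "The cumulative house index over 1 year is estimated at 2"%, and "We estimate that we can decrease the infestation-levels with 75% in the ITC intervention strategy in comparison with no intervention". From this the protocol concludes that "we need 6 clusters of 500 houses in each arm" "to demonstrate the effect of the curtain-intervention (power of 80"%). No other index is given a rate, and no significance level or sidedness is stated.
- **Indices collected in follow-up** (study components, Monitoring, Entomology): "House Index (HI), Breteau index (BI), Pupal Index per inhabitant (PPI"), at least monthly.

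**The concern.** The quantity that was powered is one member of an open list. The reader cannot tell which index, over which months, decides whether the curtains worked, and the protocol itself gives reasons to prefer different ones:

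- The introduction sets the target for new tools in terms of pupae per person, whereas the sample size uses the house index.
- Year 1 and year 2 may differ. The producer's information is that the insecticide lasts about 2 years, and the protocol plans bioassays at roughly 6-month intervals to follow its decline.
- The time plan shows entomological evaluation in columns 4 to 28. Read as months, that is 25 monthly columns, and no text says which 12 of them form the year of the cumulative index.
- The cost-effectiveness section takes its effect measure from the entomological study without naming an index, so the incremental ratio inherits the ambiguity.

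The choice of index and year can therefore be made after the results are seen. At stake are the false-positive rate of the main claim and the link between that claim and the sample size.

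**Working it through.** **1. The plan's own figure.** The protocol cites Hayes and Bennett. For unmatched clusters and proportions, clusters per arm are

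c = 1 + (z_α/2 + z_β)² × [p0(1−p0)/m + p1(1−p1)/m + k²(p0² + p1²)] / (p0 − p1)²

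Inputs from the protocol: p0 = 0.02; p1 = 0.02 × (1 − 0.75) = 0.005; m = 500; power 80%. Not stated: the significance level (two-sided 5% assumed here) and the between-cluster coefficient of variation k.

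- (1.960 + 0.842)² = 7.849
- Sampling terms: 0.02 × 0.98/500 + 0.005 × 0.995/500 = 0.0000392 + 0.00000995 = 0.00004915
- p0² + p1² = 0.000425; (p0 − p1)² = 0.000225

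| k | c | rounded up |
| --- | --- | --- |
| 0.25 | 3.64 | 4 |
| 0.40 | 5.09 | 6 |
| 0.47 | 5.99 | 6 |
| 0.50 | 6.42 | 7 |

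Six clusters follow if k lies between about 0.39 and 0.47 (two-sided 5%), or between about 0.48 and 0.56 (one-sided 5%). The figure is compatible with a 5% level but cannot be reproduced, because neither the level nor k is given. The calculation contains one index, one year and one contrast, with no allowance for further primary tests.

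**2. How many tests the wording could allow.** If the cumulative house index is taken as the house-index entry, the indices collected are three: house, Breteau and pupal. Read once, that is three tests. Read in each of two years, it is 3 × 2 = 6. Both counts are readings of the text; the protocol does not state them.

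**3. Chance of at least one false positive.** Assumptions: each test at two-sided 5%, any significant result counts as success, no true effect, and equal correlation ρ between tests (the protocol gives no correlation).

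For independent tests, 1 − 0.95ⁿ gives 1 − 0.95³ = 14.3% for three and 1 − 0.95⁶ = 26.5% for six. The indices come from the same inspections, so these are upper figures. For correlated tests the rate was simulated in two ways: as normal test statistics, and as t-tests on 6 v 6 cluster values (10 degrees of freedom).

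| Tests | ρ | normal | t, 6 v 6 |
| --- | --- | --- | --- |
| 3 | 0.5 | 12.5% | 12.8% |
| 3 | 0.9 | 8.3% | 8.7% |
| 3 | 0.95 | 7.3% | 7.6% |
| 6 | 0.5 | 20.7% | 21.7% |
| 6 | 0.9 | 10.8% | 11.5% |
| 6 | 0.95 | 8.9% | 9.4% |

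**4. What it would cost to keep several primaries.** Take k = 0.471, the value at which the formula gives exactly 6 clusters. The variance term is then 0.0001433, and √(5 × 0.000225/0.0001433) = 2.802. With Bonferroni, power per test is Φ(2.802 − z), where z is the critical value at 5%/n:

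- one test: Φ(2.802 − 1.960) = 80%
- three tests: Φ(2.802 − 2.394) = 66%; 80% would need 7.7, so 8, clusters per arm
- six tests: Φ(2.802 − 2.638) = 57% (56.5% before rounding); 80% would need 8.7, so 9, clusters per arm

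This gives every index the effect size of the house index, because the protocol offers no figure for the others. With one named primary outcome, the error rate stays at the single-test level and the 6 clusters per arm are unchanged.

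**The case against.** The strongest reply is that the plan does have a lead index. There is one primary heading, the cumulative house index is the only index named under it, and it is the only one with a rate in the sample size. The other measures appear under monitoring and are not called primary there. Multiplicity rules and the order of testing commonly sit in a statistical analysis plan, which is not at hand.

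Much of this stands, and it limits what may be said. A reader might infer three stronger things that the document does not support:

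- **That a 5% error rate on which the sample size was built is lost.** The protocol states no significance level, so 5% is an assumption throughout.
- **That success may be claimed on any one of the tests.** The protocol gives no success rule, neither any nor all. The inflated rates apply only if an any-success rule were used.
- **That there are six co-primary tests.** The yearly basis may only describe how the index is expressed, and evaluation over 2 years is compatible with a single analysis of the whole period.

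The indices also share the same house and container inspections, so the low-correlation end of the range may overstate the inflation.

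The reply does not remove the core point. The content of the primary outcome is stated in this protocol and left open by its own wording. An analysis plan that chose one index would be narrowing the protocol's definition. Giving a rate for one index suggests that it leads, but does not say that it decides.

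**Conclusion.** The point holds as a defect in the definition of the primary outcome: the index and time window that decide are not fixed, while the sample size uses one specific index, period and contrast. This rests on the text alone.

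The size is conditional. Under any-success testing at an assumed two-sided 5% per test, with ρ from 0.9 to 0.5, the false-positive chance is about 8% to 13% for three indices and about 11% to 22% for three indices in two years. At ρ = 0.95 it is still about 9% for six tests, so strong correlation reduces the excess but does not remove it. These figures show what the open wording permits. They are not the trial's actual error rate, which cannot be derived from the protocol. The change should be made, and it is a matter of wording rather than of design.

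**What to change.** In section IV.A, name a single primary outcome: the 1-year cumulative house index, compared between the ITC and no-ITC arms. It is the natural choice because it is the quantity the sample size uses. State which 12 months form the window, and state the significance level and whether it is one- or two-sided. Move the Breteau index, the pupal index and the other yearly readings to the secondary outcomes, reported with confidence intervals. Say in the cost-effectiveness section which index supplies the effect measure.

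The cost is about one paragraph of protocol text, to be settled before the outcome data are analysed. Data collection and the number of clusters do not change. The downside is that a favourable result on another index, or in year 2 alone, could no longer be presented as the primary result.

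If the sponsor prefers one prespecified analysis over the full 2 years, that also removes the ambiguity about the year. The sample-size input must then be restated as a 2-year quantity, since the 2% applies to 1 year.

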## **B. Design of intervention:**

Curtains:

The insecticide-treated curtains (ITC) to be used are made from long-lasting, insecticide treated (pyrethroid deltamethrin is applied during manufacture) polyester netting that requires no re-impregnation (PermaNet®; Vestergaard-Frandsen company). PermaNet materials are special UV protected and retain their insecticidal properties and efficacy for about 2 years (information from producer). The material has been approved by WHOPES for use as bednets. Three insecticide impregnated curtains (ITC) will be distributed in each house: 2 window curtains, cut to fit the window opening (by preference not on the window towards the street, due to street-dust and hence frequent washing needed) and 1 door curtain (to be placed in a door-opening inside the house or on the closet or on the wall where no or minimal sunshine will touch the material - if a curtain is already hanging, the project-curtain can be attached to it).

All curtains will be white patterned netting and have a 1.6m width*2.2m height size (so that people can adapt them according their window and door size).

Before distribution the consent of the users will be procured in an informed consent-form designed for this project (see annex 2).

The curtains will be distributed with an accompanying promotion campaign: a Frequent Asked Questions document (FAQ) is already elaborated (see annex 3). It will be adapted and used during this campaign, together with other context-specific promotion materials.

The curtains will be distributed to the houses, but also to public places, as working areas, schools, cultural centra will be included as far as possible.

A replacement of curtains will be foreseen for the curtains in very bad condition. If new persons are coming to live in the circumscription during the study, they will be approached for their interest to be included in the study.

Assisted community-based environmental management

Main components of this strategy:

(a) establishment of a formal task force at circumscription level to drive the environmental management activities. This group identifies, designs and implements local environmental management actions, by actively involving the community

(b) intersectoral coordination between this task force and the existing governmental structures and sectors (education, promotion, water-supply, municipal services, …)

(c) close collaboration between these task forces and the health system (especially the vector control programme).

Besides of the routine vector control programme, the assistance to set-up this intervention will be done by a local research group who will be responsible for its implementation, the coaching of the local task forces, coordination with the local health authorities, documentation of process and organization of training sessions according to the needs of the actors involved.

Distribution models for distribution of ITC

*Group I intervention*: the ITC will be distributed by the ‘operarios’ of the municipal routine vector control programme during their routine inspection visits. The communication campaign that will accompany the distribution will be designed by the municipal/provincial dengue control programme.

*Group II intervention*: The curtains will be distributed by the ‘trabajadores comunitarios’ and their local existing networks. The aim is that this model of distribution is a participatory one, where the way of distribution, promotion and communication is discussed within the existing community networks.

The Control-sites

In all areas, the routine control activities will be continued (only strategy in Group Control 1). The standard control activities are carried out by the programme’s vector control workers: entomological surveillance and source reduction through periodic inspection of houses, larviciding (with temephos) of water-holding containers, selective adulticiding (cipermethrine and clorpiriphus) when *Aedes aegypti* foci are detected, providing health education, promotion of community based environmental management and enforcing mosquito control legislation through the use of fines.

C. Study components, data collection and analysis:

1. Baseline investigation:
   1. Entomological survey:

Existing of larval and pupal surveys; the larval surveys will be conducted as in the routine system (exhaustive inspection of all houses and containers on the presence of immature stages of Aedes). The traditional Stegomyia indices will be calculated: the House Index (HI) and Breteau index (BI). The pupal surveys will consist of direct inspection inside and around all the houses following the recommendations of Focks (5). Each survey will consist of a brief questionnaire and the inspection of domestic/peridomestic areas of each house looking for potentially water-holding containers and the complete collection of mosquito pupae. The total positive containers for Ae. aegypti and their relative contribution to total pupal production will be recorded and computed. The number of persons per house will be also enquired during the application of the questionnaire for the construction of Pupal Index per inhabitant (PPI) at the cluster level and averaged on group level.

The data (positive containers) will be retrieved from the routine entomological surveillance (in the regular cycles done by VC workers), added with the foci encountered in a control visit (by independent external control workers) 1 day after the routine visit.

- 1. Opinions and expectations on ITC in the clusters that will receive ITC: Focus Group Discussions with groups of men, women and leaders separately (3 FGD per intervention group, 12 in total). Subjects: opinion on existing dengue control measures and preferences, expectations concerning the ITC, willingness to use the ITC, appropriateness of distribution channels of vector control tools. (Annex 4)
  2. Design of distribution and communication strategies: through expert- interviews:
     1. Communication experts: what are the messages that are best promoting dengue control strategies? Which are the best communication channels? How to organise best promotion in a continuous way? How to organize communication and promotion messages in a participatory way?
     2. Provincial/municipal vector control programme and community networks: exploration of best adapted and efficient distribution strategies (annex 5)
  3. Evaluation of community involvement level in dengue control activities at baseline in the 4 groups.
     1. Through Focus group Discussions with community networks and inhabitants, and through in depth interviews with inhabitants purposively sampled, data will be collected using the Rifkin-tool (already adapted to local context by Dr. [name], see annex 6 & 7) (intervention and control groups).
     2. Revision of documents:
        - Coverage of community workers
        - Existence of Community network
        - Revision of needs identification and plan of action (for environmental management activities) done by Community network
        - Revision of report of activities and risk monitoring form of Community network

1. Monitoring:
   1. Entomology:
      1. The same measurements as in the baseline entomological study will be done once intervention started (House Index (HI), Breteau index (BI), Pupal Index per inhabitant (PPI)). The frequency of the surveys will be according the cycles taking place by the routine control programme, with at least one survey per month.
      2. Repeated blocks
      3. GPS geo-referenced positioning system for follow-up of foci
   2. Epidemiology of clinical Dengue cases if an epidemic presents itself in the period of study
   3. Observation of main intra and extra domiciliary risks at household level (data collection through an existing monitoring system)
   4. Uptake and use of curtain

Uptake and its seasonal variances will be evaluated every 4 months (3 X/year) over a period of 2 years. During observation-visits in all houses, these aspects will be evaluated (Observation guide: annex 8).

- 1. Registration of executed vector control activities: information obtained from community perspective (Questionnaire: annex 9)

Every 4 months, one in 30 households will be questioned concerning the vector control activities that were realized in the previous period.

.

1. Mid-term assessments
   1. Evaluation of acceptance, use and satisfaction (curtains and implementing strategy) through household surveys, 3 and 18 months after distribution (in a sample of 330 houses/intervention arm (110 houses/circumscription, systematic random sampling)) (data collection form: annex 10)
   2. Evaluation of the adoption of the model of implementation/communication: (process evaluation) through key informant interviews (18 months after distribution)
   3. Evaluation of level of involvement of community in control actions (18 months after distribution)
   4. Persistency testing of the curtains (monitoring insecticide content of PermaNet curtains over time): This will be tested by the standard WHO cone bioassays on a sub-sample of 10 curtains after 6 months of use and subsequently at approximately 6-month intervals. (Will probably be done in LSHTM, London or LSTM, Liverpool)

**Analysis**: Two major subjects:

1. The influence of (1) individual and household characteristics, (2) model of distribution and communication and (3) community involvement level will be evaluated on the effectiveness and ITC uptake measures.
2. The influence of adding an ITC strategy will be evaluated on the community involvement process and level reached.
3. Cost-effectiveness evaluation

We collected already the financial cost of the vertical programme during the two last years preceding the intervention and will calculate the average cost per house inspected and treated.

For each arm, we will multiply the number of houses inspected and treated annually during the study by the corresponding average cost described above, to calculate the total annual cost of the routine programme per arm.

We will calculate the total economic cost of the new control tool (curtain): The financial cost of the routine programme and economic cost of the community participating in the distribution, installation and maintenance of the tools; and the economic cost of the community participating in collective vector control activities.

The total annual cost of the different arms can be obtained adding the cost of the routine programme and the economic cost of the implemented strategy.

We also will calculate the average and marginal cost per house within arms and incremental cost per house between arms.

The activities of vertical programme will be costed prospectively during two years of the study, as well as the cost regarding the distribution of the tools itself. The cost information about the installation, maintenance, and participation in collective activities will be followed by community vector control workers during their routine activities and the corresponding questions will be included in the household surveys of uptake (taking place at least every 4 months) or acceptability, in 1 out of the 30 houses in all clusters.

We will obtain the effectiveness measure from the entomological study and use the difference between the baseline data and the data for the subsequent periods as effectiveness measure.

Average cost-effectiveness will be calculated, dividing the cost by the effectiveness estimate for the corresponding period; also, incremental cost-effectiveness will be calculated by dividing the difference in total cost by the difference in effectiveness between the strategies.

The robustness of the cost effectiveness estimate we will evaluate performing the sensitivity analysis, varying the price of the community time, and using the variation observed in the correlation between the coverage of tools and the corresponding entomological outcome.

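### In the curtain clusters the delivery model and assisted community management change together, so the uptake contrast is a package effect and the curtain-by-community interaction includes the delivery difference

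*Protocol*

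**What the plan says.** **Groups.** Protocol section IV.A sets out a 2 x 2 layout. Intervention 1 (I1) is "Distribution of Curtains, no assisted community-based (CB) environmental management". Intervention 2 (I2) is "Distribution of Curtains + assisted CB environmental management". Control 1 (C1) has neither component and Control 2 (C2) has CB assistance without curtains. Annex 1 places 3 circumscriptions in each group.

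**Delivery.** Section B, under the distribution models, fixes delivery by group.
- In I1, curtains are handed out by workers "of the municipal routine vector control programme during their routine inspection visits". On communication: "The communication campaign that will accompany the distribution will be designed by the municipal/provincial dengue control programme".
- In I2, community workers and local networks distribute the curtains. "The aim is that this model of distribution is a participatory one". Communication is handled in the same spirit, under a model "where the way of distribution, promotion and communication is discussed within the existing community networks".

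**What is to be measured.** Section IV.A says the split into four groups allows measurement of "the influence of community involvement on the ITC uptake". The Analysis paragraph of section C numbers the influences to be studied, among them "2) model of distribution and communication and (3) community involvement level will be evaluated on the effectiveness and ITC uptake measures". The Introduction names the interaction between curtain distribution and the community strategy as the subject of the study.

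The protocol nowhere remarks that delivery model and CB assistance coincide.

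**The concern.** Three things change at once between I1 and I2: who brings the curtains, who shapes the communication, and whether the circumscription has assisted CB management. Uptake can be observed only where curtains are given, so I2 v I1 is the only randomised comparison that bears on it. If uptake is higher in I2, the cause could be CB assistance, the distributor, the style of promotion, or any mixture of these. Section IV.A would credit community involvement, and the Analysis paragraph would report two influences where the allocation supplies one contrast.

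This matters for use of the result. A control programme might fund CB assistance when a change of distributor would have been enough, or the reverse. A second consequence concerns the infestation indices: a curtain effect that differs between the two CB levels would be read as synergy, although the curtains were also delivered differently at those levels.

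**Working it through.** The protocol gives no figure on this point. Its sample size (6 clusters of 500 houses per arm) concerns curtains v no curtains and does not enter. The check is structural.

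**Inputs.** Group definitions come from section IV.A, delivery by group from section B, and 3 clusters per group from Annex 1.

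| Group | ITC | CB | ITC x CB | Community delivery (D) | Clusters |
|---|---|---|---|---|---|
| C1 | 0 | 0 | 0 | 0 (no curtains) | 3 |
| C2 | 0 | 1 | 0 | 0 (no curtains) | 3 |
| I1 | 1 | 0 | 0 | 0 | 3 |
| I2 | 1 | 1 | 1 | 1 | 3 |

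D stands for channel and communication together, since these also switch together. No cluster has programme delivery with CB assistance, and none has community delivery without it.

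**Uptake (6 curtain clusters).** Over I1 and I2 the CB and D columns are identical, with correlation 1.0. A model with intercept, CB and D has rank 2 for 3 parameters. If b is the effect of CB assistance on uptake and d that of delivery, then

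I2 - I1 = b + d.

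Only the sum is estimable. More clusters under the same allocation would repeat the same two rows and leave the rank at 2.

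**Infestation indices (12 clusters).** Write a for the effect of ITC under programme delivery, b for CB assistance, g for the ITC x CB interaction and d for community instead of programme delivery (b and d now on the index scale). The group means are

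- C1 = m
- C2 = m + b
- I1 = m + a
- I2 = m + a + b + g + d

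The contrasts follow:

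- C2 - C1 = b: CB without curtains, identified
- I1 - C1 = a: ITC as delivered by the programme, identified
- I2 - C2 = a + g + d: ITC as delivered by the community on top of CB assistance, identified as a package
- (I2 - I1) - (C2 - C1) = g + d: interaction plus delivery, not separable
- (I1 + I2)/2 - (C1 + C2)/2 = a + (g + d)/2: overall ITC v no ITC, averaged over two delivery models

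In the design matrix the D column equals the ITC x CB column, so intercept, ITC, CB, ITC x CB and D give rank 4 for 5 parameters. Without the interaction the rank is 4 for 4 and d becomes estimable, but only by assuming g = 0. That sets to zero the quantity the Introduction names as the subject of the study.

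**The measured involvement score.** Section C assesses community involvement at baseline and 18 months after distribution. The score can vary between clusters of one group, so it is not identical to the CB column. An uptake model with intercept, package indicator and score has 6 - 3 = 3 residual degrees of freedom, and the follow-up score is itself shaped by the allocation. For scale, a cluster-level permutation comparison of 3 v 3 has C(6,3) = 20 arrangements, so the smallest two-sided p is 2/20 = 0.10.

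**The case against.** The strongest reply has four parts.

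1. *Participatory delivery is part of community involvement, so section IV.A already means the package.* This is a fair reading of that one sentence, but the rest of the protocol does not support it. Section B defines assisted CB management by a local task force, coordination between sectors and collaboration with the health system. None of these is curtain delivery, which has its own subsection, and the Analysis paragraph numbers the two influences apart. If a package was meant, the text should say so.

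2. *Item (3) of the Analysis paragraph is a measured level, not the allocation.* This stands. A reader might infer that the involvement score is perfectly collinear with delivery, and it is not. The score analysis is possible, but it is observational and rests on 6 curtain clusters, so it does not restore a randomised separation.

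3. *Objectives 1 and 2 in section III.B are not undermined.* This also stands. Objective 1 asks about uptake in the combined and single strategies, and objective 2 about the effect of ITC alone and in combination. Both are contrasts between strategies, and the design delivers them as long as each strategy includes its delivery model.

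4. *Modelling belongs in the statistical analysis plan, and promotion is partly shared.* The choice of terms can be left to that plan, but the aliasing is fixed by allocation and delivery, and no model removes it without assuming an effect to be zero. Section B does describe a common question-and-answer document for the curtain campaign. That may narrow the communication difference, but the distributor and the party shaping the campaign still differ by group.

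**Conclusion.** The point holds in full for uptake and in part for effectiveness. On uptake, the I2 v I1 difference is the joint effect of community channel, participatory communication and CB assistance. It cannot be credited to community involvement or split between items (2) and (3). On the infestation indices, delivery is aliased with the ITC x CB interaction only.

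A reader might go further and conclude that the main result is confounded, or that no effect of CB on the house index can be identified. The protocol does not support either inference. The comparison for which the trial is sized, 6 v 6 clusters on curtains, remains estimable as an average over two delivery models, and C2 v C1 gives the CB effect without curtains. Nor must the uptake aim be dropped, since the package contrast is valid and useful.

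The conclusion assumes that delivery follows section B in every curtain cluster and that the allocation is as in Annex 1. It depends on no value for power or between-cluster variation. Severity is moderate: uptake is a secondary outcome, but the attribution as written is one the design cannot support.

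**What to change.** Change the wording of section IV.A and of the Analysis paragraph in section C:

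- Replace the claim about community involvement and uptake by: *Intervention 2 v Intervention 1 on uptake estimates the effect of one package (community channel, participatory communication and assisted CB management) against programme channel and programme campaign without assisted CB management.*
- Merge items (2) and (3), as far as they rest on allocation, into that single contrast.
- State that I1 v C1 is the effect of ITC as delivered by the programme, and I2 v C2 the effect of ITC as delivered by the community in the presence of CB assistance.
- State that any ITC x CB term includes the difference in delivery model, and that the overall ITC effect is averaged over the two models.
- Mark analyses of the measured involvement score as exploratory, being observational and, for uptake, based on 6 clusters.

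No added clusters, data or change to the interventions are needed. The cost is a narrower claim on uptake: the trial would report whether the community package differs from the programme package, without saying which component is responsible.
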